### Aim

The long-term aim is to improve the life course of MSK disorders through identification of target areas for early prevention.

### Objectives to be explored in the RCT

- 1. To estimate the effect of a motor skills intervention on aberrant movement patterns and musculoskeletal health.

### Objectives to be explored in the full cohort

1. To describe the age and sex related incidence and course of back-, neck- and extremity-disorders in a general paediatric population from three to fifteen years of age.
2. To establish potential patterns of development of musculoskeletal disorders from three to fifteen years of age.
3. To determine the potential relationship between poor motor performance and aberrant movement patterns.
4. To determine the potential relationship between motor performance at the end of preschool and musculoskeletal health throughout the school years.

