The presence of complaints from the MSK system will be reported by SMS-track. Parents will receive text messages (SMS) on a biweekly basis inquiring about the child´s MSK pain as well as observations of abnormal behaviour the past week. Replies are automatically registered and stored in an encrypted database. The system has been in use in another project in the schools of Svendborg Municipality where more than 95% of the participating families responded each week [32]. A validation study was undertaken in order to determine the reproducibility of the SMS-track reporting when comparing it with verbal reporting. The sensitivity for the SMS data was 0.98, specificity 0.87, positive predictive value 0.94 and negative predictive value 0.95, indicating high validity of data [33].

The SMS questions were developed on the basis of a qualitative study investigating how parents to children aged 3-6 years become aware of their children’s MSK pain. The study derived six themes: ‘wont/can’t use part of the body’, ‘physical signs’, ‘communicate it’, ‘demonstrate it with an outburst’, ‘change of behaviour’, and ‘protect the painful area’. A nominal group technique was used to generate the initial SMS questions and these were subsequently tested in a pilot study. The final SMS questions were:

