***Introductory SMS:***

“Dear Parents.

Thank you for participating in the project Active Children in Daycare.

In the future, you will receive 1 or 2 SMS’s every second Sunday with questions about [*child name*] muscle and joint pain in the previous 2 weeks. Pain in muscles and joints in children can be detected in many ways. Your child may tell or show it to you, hold the area or protect it and not let anyone touch it. Maybe he/she will use the body in a different way (e.g. avoiding normal movements, limp or not use one arm). It is important that you answer all SMS’s, even if [*child name*] has not had any pain.

If you have any questions to the SMS’s, please contact project coordinator [*name*] on [*telephone number*].”

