***SMS 1 (every second Sunday):***

Do you think you child have had pain from muscles or joints in the past two weeks?

Answer 1 for yes and 2 for no.

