***SMS 2 (only send out if answering ‘yes’ to SMS 1):***

How did you detect it? (Answer with numbers. You can use multiple answer options by using a comma between the numbers, e.g. 1,2)

1. [*Child name*] told or showed me

2. [*Child name*] changed the use of his/her body/arm/leg or other body part

3. [*Child name*] have had a changed mood/behaviour/sleep

Both questions will be asked during the preschool years. If the same problem is reported two consecutive times, a research assistant will call the parents and offer examination and treatment by an orthopaedic surgeon at the sports clinic at the Odense University Hospital.

Thus, the three outcomes used for analyses will be:

- - Parent-reported pain
  - Parent-reported detection of problems
  - MSK diagnoses of persistent problems

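### WP 3: the preschool SMS questions record no body site, so they cannot give site-specific incidence or course for those years, nor show that the same problem was reported twice

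*Protocol*

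**What the plan says.** All of this is in WP 3 of the Protocol.

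- **Objective.** The first objective for the full cohort is "To describe the age and sex related incidence and course of back-, neck- and extremity-disorders in a general paediatric population", covering ages three to fifteen.
- **Source of data.** Under Variables (Outcome): "The presence of complaints from the MSK system will be reported by SMS-track". The text then gives what it calls the final questions.
- **SMS 1**, sent every second Sunday: "Do you think you child have had pain from muscles or joints in the past two weeks". The reply is yes or no.
- **SMS 2**, sent only after a yes: "How did you detect it". There are three reply codes: the child told or showed the parent; the child used the body differently; mood, behaviour or sleep changed. Only the second code mentions body parts, and it pools arm, leg and the rest of the body in one answer.
- **Route to a diagnosis.** "If the same problem is reported two consecutive times", a research assistant telephones the parents and offers an orthopaedic examination.
- **Outcomes.** Three are listed: parent-reported pain, how it was detected, and diagnoses of persistent problems.
- **Analyses.** Incidence rates of musculoskeletal conditions are planned by age and sex. The number of diagnoses of persistent problems is compared between intervention groups by multilevel Poisson regression.
- **Recall.** The narrative under Variables refers to "observations of abnormal behaviour the past week". The introductory SMS refers to "muscle and joint pain in the previous 2 weeks", and SMS 1 also asks about two weeks.

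**The concern.** The objective names three body regions, but the instrument that is to report musculoskeletal complaints cannot tell them apart. This is not a detail that an analysis plan could settle later, because a variable that was not collected cannot be derived afterwards. If the plan is followed as written, the preschool part of objective 1 can be answered only for pain at any site, with site added for those children who happen to be examined.

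The second problem reaches the randomised comparison. The diagnosis count depends on a condition about repeated reports of one problem, and the recorded replies do not contain what is needed to check it. The ascertainment rule for an outcome compared between arms is therefore not defined in terms of recorded data.

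**Working it through.** No sample size, power or event figure bears on this point, so the check sets the text of WP 3 side by side.

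**Step 1: does any recorded reply carry a site?** SMS 1 yields one binary value with no site. SMS 2 yields one or more of three codes for how the pain was noticed. Code 1 has no site. Code 2 pools all body parts. Code 3 concerns mood, behaviour or sleep. Back, neck and extremity cannot be separated by any combination of replies.

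**Step 2: is there another source of site in the preschool years?** Of the three listed outcomes, the first two are the SMS replies from step 1. The third, a diagnosis after examination, would normally carry a site. To enter it, a child must have a problem reported in two consecutive fortnightly rounds, and the parents must accept the offered examination. Short episodes and declined examinations are therefore absent, so a rate built on these diagnoses describes persistent, examined problems and not all incident disorders of a region.

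**Step 3: can the replies identify a repeat of one problem?** Take two consecutive rounds and three illustrative histories:

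- One knee pain lasting through both rounds, told by the child each time: SMS 1 = yes, yes; SMS 2 = 1, 1.
- A knee pain in the first round and a new neck pain in the second, told by the child each time: SMS 1 = yes, yes; SMS 2 = 1, 1.
- One knee pain lasting through both rounds, noticed first as a limp and later told by the child: SMS 1 = yes, yes; SMS 2 = 2, 1.

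The first two histories differ but give identical data. The first and third are the same problem but give different data. Agreement of the SMS 2 codes is thus neither sufficient nor necessary for the problem to be the same.

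**Step 4: which years are affected?** The two questions are stated to be asked during the preschool years. Length of follow-up is 12 years, of which 9 are in school, so the point is shown for 12 − 9 = 3 years. The musculoskeletal questions for the school years are not given.

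**Step 5: recall.** The narrative says one week. Both texts that parents receive say two weeks, which matches the fortnightly sending. The mismatch lies in the narrative.

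**The case against.** Several counter-arguments have force.

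- *WP 3 as a whole may still deliver objective 1.* A reader might infer that site is never recorded and that the objective fails through age fifteen. The document does not support that. The two questions are limited to the preschool years, the school-age questions are not shown, and diagnoses would normally name a site.
- *The list of regions may only describe what musculoskeletal disorders cover.* The planned incidence analysis has no site breakdown, which fits this reading. The wording of the objective fits a site-specific reading at least as well. If the broader meaning is intended, the objective should say so.
- *The caller can ask whether it is the same pain.* This is possible, and nothing in the text says that callers guess. The diagnosis is made at the examination, so two unrelated pains do not by themselves create one. What stands is narrower: the protocol does not say that the caller asks or records this, and the condition comes before the call.
- *Objective 2 looks affected too.* It names no body site, and the latent class analyses can be run on repeated all-site reports. It is not part of this point.
- *The one-week wording might suggest that half of the follow-up time goes unobserved.* Both parent texts cover the full fortnight, so no such loss follows. The phrase "as well as observations of abnormal behaviour the past week" may in any case attach only to behaviour and not to pain.
- *Parents of young children may not be able to give a valid site.* The questions came from a qualitative study, a nominal group technique and a pilot, and a site item has not been tested here. This is a reason to re-test a new item, or to narrow the objective instead.

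**Conclusion.** The point holds for the preschool years and for cohort objective 1. The fixed SMS questions cannot supply incidence or course by back, neck and extremity in that period. Only diagnosed persistent problems could carry a site, and these are a selected subset. The replies also cannot establish that one problem was reported twice in a row, which is the only described route to the diagnosis count compared between groups.

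The size cannot be put as a percentage, because the document gives neither the share of episodes that persist over two rounds nor the uptake of the examination. In kind, site is missing for every preschool episode that does not lead to an examination. Bias in the between-group comparison is not shown; what is shown is an ascertainment condition that the recorded data cannot verify.

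The conclusion assumes that the objective means separate regions and that no other preschool source of site exists outside the text at hand. WP 3 refers to none, but the main protocol is not shown. The recall mismatch is a wording slip and adds no weight.

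**What to change.** 1. Add one numeric body-site reply (back, neck, arm, leg, other) to SMS 2, which goes out only after a yes. The cost is slight extra burden for those parents and a brief re-test of the wording.
2. If the item is not added, restrict objective 1 for the preschool years to musculoskeletal pain at any site plus diagnosed persistent conditions. This costs only text, but gives up site-specific results for non-persistent episodes at those ages. If site is already recorded elsewhere, say where.
3. Reconcile the condition on repeated reports of one problem with what the SMS actually records, so that entry to the diagnosis count can be verified from the data. No referral rule is proposed here.
4. Align the one-week wording in the WP 3 narrative with the two-week recall in the introductory SMS and SMS 1. This is an editorial change.

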### Variables

Predictors

- Motor performance as described under ‘core outcomes for all WP’s’
- Movement patterns will be evaluated by kinematic analyses of Drop Vertical Jump Test and Standing Broad Jump Test.

*Drop Vertical Jump Test*

The Drop Vertical Jump Test (DVJ) is a validated clinical test, in which kinematics around the knee are assessed during an accelerated vertical jump from a 31-cm. high box, landing on both feet and immediately followed by vertical jump as high as possible (11). Aberrant movements, including increased valgus motion, high abduction loads, and increased internal rotation of the hip, has repeatedly been shown as a risk factor for (a) anterior cruciate ligament rupture among female athletes (11), and (b) development of patella femoral pain syndrome among female athletes (23, 24) and military recruits of both sexes (25).

*Standing Broad Jump Test (a.k.a. Horizontal Long Jump Test)*

The Standing Broad Jump Test (SBJ) is performed by having the child stand behind a line on the floor, jumping as far as possible, and the length of the jump is measured. It is considered a simple, cheap and safe test, suitable for the assessment of lower body maximal strength in adolescents (26). SBJ has been tested on children as young as 5 years of age, and found to have normally distributed total scores and good reliability (ICC=0.88) (27). Furthermore, it has been used to monitor children with either low or high motor competence with significant discriminative abilities over a 5 years’ period (28).

*Measurement equipment*

The DVJ and SBJ tests will be measured using the Captury motion capture system ([www.thecaptury.com](http://www.thecaptury.com)). The Captury is a portable 8-camera high-speed motion capture system which makes no use of any markers, suits or special hardware. A child avatar has been specially developed to be used in the present project in collaboration with Institute of Sports Science and Clinical Biomechanics, University of Southern Denmark. The Captury has been found to be reliable compared to the Vicon motion capture system used as gold standard (unpublished data, article under preparation).

Outcome

The presence of complaints from the MSK system will be reported by SMS-track. Parents will receive text messages (SMS) on a biweekly basis inquiring about the child´s MSK pain as well as observations of abnormal behaviour the past week. Replies are automatically registered and stored in an encrypted database. The system has been in use in another project in the schools of Svendborg Municipality where more than 95% of the participating families responded each week [32]. A validation study was undertaken in order to determine the reproducibility of the SMS-track reporting when comparing it with verbal reporting. The sensitivity for the SMS data was 0.98, specificity 0.87, positive predictive value 0.94 and negative predictive value 0.95, indicating high validity of data [33].

The SMS questions were developed on the basis of a qualitative study investigating how parents to children aged 3-6 years become aware of their children’s MSK pain. The study derived six themes: ‘wont/can’t use part of the body’, ‘physical signs’, ‘communicate it’, ‘demonstrate it with an outburst’, ‘change of behaviour’, and ‘protect the painful area’. A nominal group technique was used to generate the initial SMS questions and these were subsequently tested in a pilot study. The final SMS questions were:

***Introductory SMS:***

“Dear Parents.

Thank you for participating in the project Active Children in Daycare.

In the future, you will receive 1 or 2 SMS’s every second Sunday with questions about [*child name*] muscle and joint pain in the previous 2 weeks. Pain in muscles and joints in children can be detected in many ways. Your child may tell or show it to you, hold the area or protect it and not let anyone touch it. Maybe he/she will use the body in a different way (e.g. avoiding normal movements, limp or not use one arm). It is important that you answer all SMS’s, even if [*child name*] has not had any pain.

If you have any questions to the SMS’s, please contact project coordinator [*name*] on [*telephone number*].”

***SMS 1 (every second Sunday):***

Do you think you child have had pain from muscles or joints in the past two weeks?

Answer 1 for yes and 2 for no.

***SMS 2 (only send out if answering ‘yes’ to SMS 1):***

How did you detect it? (Answer with numbers. You can use multiple answer options by using a comma between the numbers, e.g. 1,2)

1. [*Child name*] told or showed me

2. [*Child name*] changed the use of his/her body/arm/leg or other body part

3. [*Child name*] have had a changed mood/behaviour/sleep

Both questions will be asked during the preschool years. If the same problem is reported two consecutive times, a research assistant will call the parents and offer examination and treatment by an orthopaedic surgeon at the sports clinic at the Odense University Hospital.

Thus, the three outcomes used for analyses will be:

- - Parent-reported pain
  - Parent-reported detection of problems
  - MSK diagnoses of persistent problems

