### Covariates

The following covariates will be accounted for when analysing the results: sex, age, socioeconomic status, child well-being and parental MSK health.

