### Analyses

Multilevel logistic regression will be conducted to determine if there was a difference in aberrant movement problems by intervention group after adjusting for time in intervention, imbalanced covariates from WP1, school and socioeconomic status of the school.

Multilevel Poisson regression will be conducted if the number of MSK diagnoses of persistent problems differs by intervention group after adjusting for time on intervention, imbalanced covariates from WP1, school and socioeconomic status of the school.

The age-specific, sex-specific and age- and sex-specific incidence rate of MSK conditions will be calculated.

Longitudinal latent class analysis and latent class growth analysis will be conducted to describe the MSK developmental patterns. The sequential model comparisons (T classes vs. T + 1 classes) and chi-square goodness-of-fit test will be evaluated using the parametric bootstrapping technique. Lastly, the associations between class membership and the prevalence of related measures will be examined using a confirmatory latent class analysis approach.

Multilevel longitudinal logistic regression analyses will be conducted to determine if poor motor performance is associated with aberrant movement patterns after adjusting for age, sex and other important covariates. The interaction between time and poor motor performance will be examined.

Multilevel longitudinal Poisson regression analyses will be conducted to determine if motor performance at the end of preschool is predictive of the number of MSK diagnoses throughout the school years after adjusting for age, sex and other important covariates. The interaction between time and motor performance will be examined.

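### WP 3 compares diagnosis counts between arms, but the only preschool route to a diagnosis it describes is an accepted offer of examination, so any difference in uptake between arms would pass into the rate ratio

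*Protocol*

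**What the plan says.** The protocol, WP 3, Variables (text under SMS 2), sets out a sequence. The trigger is a repeated report: "If the same problem is reported two consecutive times". Then "a research assistant will call the parents and offer examination and treatment by an orthopaedic surgeon". The section goes on to list three outcomes as the consequence of this procedure: parent-reported pain, parent-reported detection, and "MSK diagnoses of persistent problems". It describes no other source of preschool diagnoses and gives no rule for a triggered problem whose parents decline or cannot be reached.

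WP 3, Analyses, gives the comparison: "Multilevel Poisson regression will be conducted if the number of MSK diagnoses of persistent problems differs by intervention group". As printed, the sentence makes the model conditional on a difference; I take it to mean that the model tests for one. The estimate is to be taken "after adjusting for time on intervention, imbalanced covariates from WP1, school and socioeconomic status of the school". WP 3, Covariates, names "sex, age, socioeconomic status, child well-being and parental MSK health". Neither list includes contact with the parents or acceptance of the offer.

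The same Analyses section gives one other model by intervention group, for aberrant movement. It names no between-arm model for parent-reported pain or detection.

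**The concern.** The RCT objective of WP 3 has two parts, movement patterns and musculoskeletal health. For the second part, the diagnosis count is the only outcome with a stated between-arm model. A child enters that count after four steps: a persistent problem, two parent reports, a successful call, and an accepted examination. The treatment effect of interest concerns the first step. The third and fourth are parental behaviour, and nothing in the model separates them from the first.

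Parents who know that their preschool runs a motor skills programme may be more or less inclined to take up an examination. Any such difference would appear in the rate ratio as an effect of the programme, or would hide one. The reported result could not tell the two apart unless uptake is shown by arm.

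**Working it through.** **Inputs.** The protocol gives no sample size, event rate or acceptance rate for this outcome, so there is no planned figure to reproduce. Its only response figure, "more than 95% of the participating families responded each week", comes from another project and concerns replies to text messages, not attendance at a hospital examination. All uptake rates and event counts below are assumptions.

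**1. Effect on the rate ratio.** Let λ be the rate of persistent problems that an examination would confirm, and u the proportion of these whose parents are reached and accept. Expected diagnoses per child are λ × u, so

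observed rate ratio = (λ₁/λ₀) × (u₁/u₀) = true ratio × uptake ratio.

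With no true effect (λ₁/λ₀ = 1), intervention against control:

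- 80% against 80%: 0.80/0.80 = 1.00
- 75% against 80%: 0.75/0.80 = 0.94
- 70% against 80%: 0.70/0.80 = 0.875
- 60% against 80%: 0.60/0.80 = 0.75
- 80% against 70%: 0.80/0.70 = 1.14

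The bias can also hide a benefit: a true ratio of 0.80 with uptake of 75% against 60% gives 0.80 × 0.75/0.60 = 1.00.

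**2. Effect on the test.** Take a two-sided 5% Wald test on the log rate ratio of two independent Poisson counts, SE = √(1/d₀ + 1/d₁). With 100 true problems per arm and uptake of 80% (control) against 70% (intervention), d₀ = 80 and d₁ = 70. Then SE = √(1/80 + 1/70) = 0.164, ln 0.875 = −0.134, and the shift is 0.134/0.164 = 0.82 standard errors. The chance of a significant result with no true effect is Φ(−1.96 + 0.82) + Φ(−1.96 − 0.82) = 12.9%. For other numbers of true problems per arm:

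| Uptake, control vs intervention | 50 | 100 | 200 | 400 |
|---|---|---|---|---|
| 80% vs 80% | 5% | 5% | 5% | 5% |
| 80% vs 70% | 8.9% | 12.9% | 21.1% | 37.2% |
| 80% vs 60% | 22% | 39% | 66% | 92% |

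These figures ignore clustering by preschool. A correct multilevel model has a larger standard error, so for the same counts the percentages would be lower. The rate ratios in step 1 do not depend on this.

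**3. Loss of events when uptake is equal.** The Poisson part of the variance scales with 1/u. Losing 20% of events multiplies the SE by 1/√0.8 = 1.118, and losing 30% by 1/√0.7 = 1.195. These are upper limits: the between-preschool part of the variance does not grow when events are lost, so the inflation is smaller in the clustered model.

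**4. Can the trigger be counted from the SMS data?** SMS 1 records yes or no for pain. SMS 2 records how the parent noticed it, not where it was. The replies can show two consecutive positive answers, but cannot by themselves show that both concern the same problem. A count of triggered episodes therefore needs its own definition.

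**The case against.** The strongest reply is that the bias is conditional and nothing in the file shows that it will occur. The same trigger and the same offer are described for all children, and with equal uptake the rate ratio is unaffected. That stands. A reader might infer that the comparison is already biased, or that the arms are known to be unmasked. The documents support neither. Masking of parents is not stated in this file, which refers to a main protocol that is not shown. Parental awareness is an inference from WP 6, Background, where the programme is part of the preschool curriculum, and from the RE-AIM table in WP 2, where next of kin are asked about their satisfaction.

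A reader might also infer that a declined examination is coded as zero. That is the natural reading of a count of diagnoses, but it is not written, and a rule may exist in an analysis plan.

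Nor does uptake that varies with socioeconomic status settle the matter. In a randomised comparison it biases the arm contrast only if status is unbalanced or alters how allocation affects uptake, and status is among the adjustment variables.

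Finally, one might want to put an SMS-based count in place of the diagnosis count. The documents do not support going that far. If parents know the arm, their SMS reports can differ by arm too, and a parent report is less specific than a surgeon's diagnosis. The diagnosis count already depends on those reports, however, so a parallel SMS count brings in no arm-related selection that is not already present.

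What remains is that the protocol itself fixes the outcome, the described route to it, the model and the adjustment set, and that this combination cannot separate an effect on problems from an effect on uptake.

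**Conclusion.** The point holds in conditional form. The only described preschool route to a WP 3 diagnosis runs through an accepted offer, and the between-arm model does not account for contact or acceptance. If uptake differs by arm, the rate ratio is multiplied by the uptake ratio: 0.875 at an assumed 70% against 80%, and 0.75 at 60% against 80%. If uptake is equal, there is no bias and the cost is precision, at most about 12–20% on the standard error for a 20–30% loss of events.

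This rests on three assumptions: that no undisclosed second route supplies preschool diagnoses, that unexamined problems contribute no diagnosis, and that the chance of confirmation at examination is the same in both arms. It concerns one work-package outcome, not the trial's primary outcome, and not parent-reported pain or detection, neither of which requires an examination. It is worth correcting because this is the only musculoskeletal-health outcome in WP 3 with a stated comparison between arms.

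**What to change.** Keep the surgeon-diagnosis count and its model. In WP 3, Analyses:

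- Add a parallel between-arm multilevel Poisson analysis of SMS-triggered persistent episodes, with the same adjustment, counted for every child whether or not an examination took place.
- Define the episode from the SMS data, for example as two consecutive positive answers to SMS 1, because SMS 2 does not record the site of the pain.
- Report by arm the number of offers made, parents contacted and examinations carried out.
- State that the diagnosis rate ratio will be read as a treatment effect only if the two analyses agree or uptake is similar in the arms.

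The cost is small. The SMS replies are already stored, and the study must identify each trigger in order to make its calls, so the addition is a log of contact and attendance plus one further model. The drawback is that the added count is parent-reported, less specific than a diagnosis, and still open to reporting that differs by arm. The offer of examination to families is unchanged.
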